**Figure 4 F4:**
[figure not shown]
**Conceptual model for the effects of maternal and infant geohelminth infections on asthma in children**. The effects of these exposures on asthma are considered to occur via effects on bronchial hyperreactivity. The protective effects of chronic helminth exposures (maternal and infant infections within the first 2 years of life) are presumed to occur via the development of a modified Th2 (mTh2) response that may affect bronchial hyperreactivity through: 1) Immune regulation/suppression-suppression of airways inflammation via enhanced production of geohelminth or aeroallergen-induced IL-10. 2) Homeostasis-enhanced production of spontaneous IL-10 will suppress airways inflammation non-specifically. Alternatively children without early geohelminth exposures and that are first exposed to infection after 2 years of age (> 24 m) may respond to *A. lumbricoides *infection with strong inflammatory responses in the airways that up-regulate pro-inflammatory pathways including Th1, Th2, and Th17. The modified Th2 response will be defined by the presence of specific IgG4 antibodies to geohelminths. RTIs- respiratory tract infections. ETS-environmental tobacco smoke.

**Figure 5 F5:**
[figure not shown]
**Conceptual model for the effects of maternal geohelminth infections on eczema**. Effects of maternal geohelminth exposures on eczema are considered to occur through the capacity of the immune system to regulate inflammation of the skin caused by external insults. Factors that may determine the ability of the immune system to do this include: 1) Immune maturation-the speed of maturation of the immune response in early life is likely to effect the ability of the immune response to respond to infections and other insults with appropriate but measured inflammatory responses. 2). Immune regulation/suppression-the development of robust and specific immune regulatory mechanisms are important for the development of an appropriate inflammatory response to specific insults. 3) Immune homeostasis-robust mechanisms to limit responses to pro-inflammatory stimuli may be an importance mechanism for the control of inflammation.

### Information, ethical approval, consent, and ethical considerations

The Ministry of Health in Ecuador was informed of the study and gave its support for the study in Esmeraldas Province, Ecuador (Subsecretaria General de Salud, reference SSG-10-000285). Formal recruitment into study occurred at the first home visit done during before the child was 14 days old. Informed consent for the collection of samples during the study before this time was done at 2 different time points: 1) antenatal clinic visit for collection of a stool and blood samples: 2) in the maternity department of HPAB for collection of maternal stool and blood samples, cord blood and meconium. At each of the three times at which written consent was obtained, the mother received both written and verbal information in Spanish on the aims of the study and the reasons for collection of study samples. Results are provided to the mother for all clinical samples collected. Where necessary, the child will be evaluated by a study physician, and appropriate medication and nutritional supplements provided as required through the ECUAVIDA study clinic at HPAB. Appropriate antiparasite treatment is given for all stool samples with documented geohelminth infections. Benzimidazole drugs are not given to pregnant women or children before 2 years of age following the recommendations of the Ecuadorian Ministry of Health. Infected mothers are offered albendazole when breast-feeding has finished. Infected children aged below 2 years are treated with pyrantel and after 2 years with albendazole. Infections with *Giardia intestinalis *and *Entamoeba histolytica *are treated with a standard course of metronidazole if characteristic trophozoites are observed. The study protocol was approved by the Ethics Committees of the Hospital Pedro Vicente Maldonado and the Universidad San Francisco de Quito, and is registered as an observational study (ISRCTN 41239086).

Although anthelmintic treatment is a highly popular intervention, clear health benefits from the treatment of pregnant women have not been unequivocally demonstrated, and such benefits could be argued to be at best marginal in most endemic regions where hookworm anaemia is relatively infrequent and geohelminth infections are low intensity [61]. For this reason, we opted for an observational rather than an interventional design that would allow us to understand the natural history of the interaction between early geohelminth exposures and the study outcomes, but provide the opportunity to identify potential interventions that could be beneficial and be evaluated in future intervention studies.

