### Hypotheses

This study has been designed to investigate four specific hypotheses relating to the effect of maternal and infant infections with geohelminths on host immune responses and development of allergic inflammatory diseases: 1) chronic exposures to geohelminth infections (i.e. maternal geohelminth infections and infant geohelminth infections within the first 2 years of life) suppress immune responses to childhood vaccines; 2) chronic exposures to geohelminth infections suppress aeroallergen skin test reactivity; 3) chronic exposures to geohelminth infections protects against the development of eczema; and 4) chronic exposures to geohelminth infections protect against the development of asthma but non-chronic exposures (i.e. later childhood exposures occurring after 2 years in the absence of maternal geohelminth infections) increase the risk of asthma.

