### Measurement and definition of geohelminth exposures

Stool samples to measure geohelminth infections have been collected from mothers in the third trimester of pregnancy (stool samples collected after birth and before the child is 14 days old are considered to represent a third trimester stool sample where the mother has not received anthelmintic treatment) and from infants at 3, 7, 13, 18, 24, and 30 months, and at 3, 5, and 8 years. Stool samples are analysed using a combination of standard methods including direct saline mounts, the modified Kato-Katz method, formol-ether concentration, and carbon-coproculture methods [45]. Geohelminth infectious exposures will be defined as follows: 1) maternal geohelminth infections-presence of any geohelminth infection detected during the 3^rd ^trimester of pregnancy; and 2) infant geohelminth infections-presence of any geohelminth infections detected during the first 2 years of life.

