### Potential effects of geohelminth infections on allergic sensitization

Childhood geohelminth infections are inversely associated with allergen skin test reactivity [81-87]. This observation has led to the suggestion that anti-parasite immune modulatory mechanisms may suppress allergic inflammatory responses to aeroallergens. However, the findings of intervention studies in which children infected with geohelminths have received anthelmintic treatment are contradictory. Different intervention studies have provided evidence for an increased incidence [88] or prevalence [55,89,90] of allergen skin test reactivity after periodic anthelmintic treatments, but a large cluster-randomized trial of periodic anthelmintic treatment in Ecuador did not observe a change in the prevalence of allergen skin test reactivity after treatment [91]. The contradictory findings of different studies could be explained by differences in the prevalence of geohelminth parasites between different geographic regions, the period for which anthelmintic treatment was given, the effects of early exposures to geohelminths in programming anti-allergic responses [5,39], or treatment effects on other endemic helminth infections (e.g. *Toxocara*).

The presence of geohelminths during pregnancy may modify the immune responses of offspring *in utero *[41]. The possible protective effects of environmental exposures such as geohelminths against allergy may be strongest when they occur in the first year or two of life [92]. We have hypothesized that early exposures to geohelminths may programme the infant immune system for reduced allergy [39]. Such programming may not be reversible (i.e. by anthelmintic treatment in later childhood) and could be 'reinforced' later by active regulatory mechanisms induced by heavy helminth infections (reversible by anthelmintic treatment) [39]. Evidence in support of this hypothesis has come from a recent observational study in Brazil showing that early and heavy exposures to *T. trichiura *protected against allergen skin test reactivity later in childhood independent of later infections [93].

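### The infant exposure is one detected infection, treated on detection, but it is labelled and interpreted as chronic infection

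*Protocol article*

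**What the plan says.** The section on measurement and definition of geohelminth exposures defines the exposure as "infant geohelminth infections-presence of any geohelminth infections detected during the first 2 years of life". It sets no condition on duration, repeat positives or intensity. Stools are collected "from infants at 3, 7, 13, 18, 24, and 30 months, and at 3, 5, and 8 years", so five scheduled samples (3, 7, 13, 18 and 24 months) fall in the exposure window. The note under Table 2 counts the exposure the same way, as at least one documented infection.

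The section on ethical approval and consent says "Appropriate antiparasite treatment is given for all stool samples with documented geohelminth infections", and for children "Infected children aged below 2 years are treated with pyrantel and after 2 years with albendazole". For mothers it says "Infected mothers are offered albendazole when breast-feeding has finished".

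The Hypotheses section frames its predictions in terms of "chronic exposures to geohelminth infections (i.e. maternal geohelminth infections and infant geohelminth infections within the first 2 years of life". The captions to Figures 3 and 4 attribute the expected protective effects on skin tests and asthma to a modified Th2 response that arises with chronic infection or exposure. The Analysis plan uses maternal or infant infection as the primary contrasts, in logistic regression.

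**The concern.** In the first two years, a documented infection is both what makes a child exposed and what triggers treatment. The infant variable cannot separate the two.

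The article's own biology makes this matter. The Background says that initial exposures may go with enhanced allergic inflammatory responses to the parasite, whereas long-term infection and repeated exposure bring tighter control. A child positive once at 13 months and treated is coded the same as a child positive at several visits, although the model expects these states to differ.

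The hypotheses concern chronic infection, but the variable measures any infection that was found and treated. A weak or null infant result could then be read as evidence about untreated chronic infection in infancy. The Discussion says the study is to inform policy on anthelmintic drugs in pregnancy and infancy, so that misreading would have consequences.

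**Working it through.** **1. Where the mismatch lies.**

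| Element | Section | Content |
|---|---|---|
| Exposure | Measurement and definition of geohelminth exposures | one detected infection to 2 years is enough |
| Treatment | Ethical approval and consent | every documented infection is treated, including below 2 years |
| Label | Hypotheses | chronic exposure |
| Mechanism | Figures 3 and 4 | depends on chronic infection |
| Biology | Background | initial and long-term or repeated exposures act differently |

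**2. Which rows are touched.** Table 2 has 14 rows: 8 maternal and 6 infant. The last infant row (N = 1,207, 20% exposed, 25% vs 15%) reverses the direction of effect and looks like the later-exposure part of the asthma hypothesis. The calculations below use the other five. Maternal third-trimester infection is not treated until breast-feeding has finished, so the maternal rows are largely spared.

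**3. Reproducing the stated power.** Infant infection and asthma at 5 years: N = 1,725, 35% exposed, 17% vs 23%, alpha 0.05 (two-sided assumed), stated power 83%.

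- n1 = 1,725 × 0.35 = 603.75; n2 = 1,121.25; 1/n1 + 1/n2 = 0.002548
- pooled p = 0.35 × 0.17 + 0.65 × 0.23 = 0.209
- SE0 = √(0.209 × 0.791 × 0.002548) = 0.02053
- SE1 = √(0.17 × 0.83/603.75 + 0.23 × 0.77/1,121.25) = 0.01979
- z = (0.06 − 1.96 × 0.02053)/0.01979 = 1.00, so power = 84% (82.5% with a continuity correction)

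The stated 83% is reproduced. The other four early-infection rows also come within 2 points of their stated values, so the arithmetic in these rows is not at fault.

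**4. What dilution would do.** Let f be the share of the assumed effect that is lost. The exposed proportion becomes p1(f) = p2 + (p1 − p2)(1 − f). The article gives no value for f, so each value here is an assumption. For asthma:

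- f = 0.10: p1 = 0.176, difference 0.054, SE0 = 0.02060, SE1 = 0.01995, z = 0.68, power 75%
- f = 0.25: p1 = 0.185, difference 0.045, SE0 = 0.02071, SE1 = 0.02019, z = 0.22, power 59%

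The same calculation for all five rows, at each row's own sample size and alpha:

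| Infant row | f = 0 | 0.10 | 0.25 | 0.50 |
|---|---|---|---|---|
| Asthma, 5 years | 84% | 75% | 59% | 30% |
| HBV, 5 years | 96% | 91% | 76% | 37% |
| Skin test, 3 years | 99% | 98% | 88% | 44% |
| OPV type 3, 5 years | >99% | >99% | 98% | 73% |
| TT, 5 years | >99% | >99% | 99% | 83% |

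The effect is uneven. The asthma row drops below 80% at 10% dilution, while TT stays above 80% even at 50%. The note to Table 2 says its asthma effect comes from cross-sectional analyses, and the article describes no allowance for treatment at detection.

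**The case against.** The strongest defence is that chronic is a defined label. The Hypotheses section spells it out and contrasts it with first exposure after 2 years in the absence of maternal infection. On that reading it is a matter of timing and agrees with the exposure definition. This stands as far as the two definitions go. It does not cover the figure captions and the Background, where the word carries duration and the expected effect depends on it. Figure 4 does offer specific IgG4 as a marker of the modified Th2 response, but that marker is not part of the exposure definition.

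Four stronger readings are tempting, and the article does not support them.

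- *The article itself says treatment removes the effect.* A reader might infer this from the statement that early programming "could be 'reinforced' later by active regulatory mechanisms induced by heavy helminth infections (reversible by anthelmintic treatment". The same sentence first says that the programming may not be reversible by treatment in later childhood, and it ties reversibility to later, heavy infections. Dilution is plausible, not established.
- *Treatment contradicts the natural-history aim outright.* The design is said to "allow us to understand the natural history of the interaction between early geohelminth exposures and the study outcomes", but that sentence follows an argument about treating pregnant women, whose infection is untreated at the time. At most, the phrase fits the infant exposure poorly.
- *Unexposed children are missed, untreated infections.* They are children with no infection found on scheduled stools examined by several methods. No miss rate is given, and most may be uninfected.
- *No infant infection lasted beyond about six months.* The longest gap between scheduled stools in the window is 6 months (7 to 13, and 18 to 24). The bound also needs a truly negative previous stool, attendance at each visit, and cure without reinfection.

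It is also fair to say that further exposure codings are often left to a full protocol or analysis plan. The absence of a graded coding is therefore not the finding. The finding is the conflict between a stated definition, a stated label and a stated treatment rule.

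**Conclusion.** The point holds as a mismatch between exposure, label and interpretation, confined to the infant contrast. As defined, that contrast compares infection detected and treated with no infection detected, and it pools single with repeated infection. Relative to the chronic infection in the hypotheses, the estimate is plausibly pulled toward the null. The amount cannot be derived from the article. On assumed losses of 10% and 25%, power for infant infection and asthma at 5 years falls from 84% to 75% and 59%; the TT and OPV type 3 rows tolerate such losses. These figures are unadjusted two-group comparisons at the 35% exposure used in Table 2. At the roughly 30% given in the note below the table, the asthma row would start from 81%. The treatment policy itself is not in question.

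**What to change.** Reconcile the exposure definition, the hypotheses and the treatment statement:

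- Describe the infant exposure as any infection detected and treated in the first 2 years, and stop using chronic as the label for a single positive stool.
- Pre-state an additional graded exposure from the scheduled stools to 24 months: 0, 1, or 2 or more positive visits. Keep the word repeated for two or more, and note that this group may reflect reinfection or treatment failure rather than untreated persistence.
- State that infant results do not by themselves support conclusions about untreated chronic infection in infancy.
- Keep any breakdown by treatment received after 24 months descriptive. That treatment is triggered by later infection, so stratifying on it would condition on an event after the exposure.

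The cost is wording and one further coding of stools already scheduled. The group with two or more positives will be smaller and its estimate less precise. No change to treatment is proposed.

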## Discussion

The ECUAVIDA cohort study has been designed to investigate the potential impact of early exposures to geohelminth infections during pregnancy and in the first 2 years of life on protective immunity provided by widely used infant vaccinations and on the development of allergic sensitization and allergic diseases. The present study is one of several observational and intervention studies [18,35] currently in progress that will inform public health policy of the potential effects of early exposures to these parasites on a number of health outcomes and the potential benefits as well as risks of providing anthelmintic drugs during pregnancy and infancy in areas where these parasites remain highly prevalent. Adequate evidence to support changes in public health policy will require studies to be conducted in different geographic settings and among different populations with varying prevalence of geohelminth parasites.

### Potential effects of geohelminth infections on vaccine immune responses

Currently, the most effective public health intervention aimed at reducing infectious disease deaths in under-5s is infant vaccination. Several vaccines are recognized to be less immunogenic in poor populations [7,8,10,62-66] requiring an increase in the dose or number of doses administered to achieve adequate vaccine immunity [7,67]. Poor vaccine immunogenicity is a problem for mucosal vaccines such as OPV and rotavirus both of which have proved to be less immunogenic in poor compared to wealthier populations [9,10,68,69]. In the case of OPV, poor vaccine immunity is most marked to OPV type 3 [7,70,71], and as many as 11 doses of OPV may be required to achieve 90% seroconversion [72]. Factors contributing to poor responses to vaccines may include overcrowding, poor sanitation, high-titer maternal antibodies, micronutrient malnutrition, environmental enteropathy and co-infections [8,73,74]. The relative importance of these factors in affecting vaccine immune responses may vary between vaccines.

Geohelminth infections have deleterious effects on vaccine immunity to oral [32,75] and parenteral vaccines [30,31] in children, and there is growing evidence from experimental animal models that concurrent parasite infections have important suppressive effects on vaccine immune responses [25,76,77]. Most human studies to date have been conducted in school age children or adults. There are few data from studies investigating the effects of maternal geohelminth infections on vaccine immune responses in infancy. Such studies have evaluated effects of maternal helminth infections and have provided evidence for a suppressive effect of maternal infection on IFN-γ responses to mycobacterial antigens in newborns [40] and IgG antibody responses to *Haemophilus influenzae *type b vaccine (Hib) at 6 months of age [31].

The immunological mechanisms by which such infections mediate these effects are poorly understood. Geohelminth exposures may suppress vaccine immune responses through three possible immunological mechanisms (Figure 2): 1) Th2 polarization-with a switch in Th1 towards Th2 responsiveness causing reduced Th1 responses (i.e. IFN-γ) responses important for antiviral immunity and immunity against bacterial infections (e.g. *Mycobacteria *[78]*and Bordetella pertussis *[79]). Such a mechanism would predict an overall and non-specific Th2-biassed response to both vaccine and other antigens with a failure to develop 'protective' Th1 vaccine responses. 2) Immune homeostasis-attenuated immune responses caused by strong homeostatic mechanisms such as increased spontaneous production of IL-10 associated with chronic geohelminth infections [80]. Such effects would be expected to suppress Th1 and Th2 immune responses to vaccines and may result in an increased threshold for the activation of immune responses. 3) Immune suppression-this could be antigen-specific or caused by bystander suppression. Previous studies have demonstrated that the suppression of immunity to TT in vaccinated subjects infected with *Onchocerca volvulus *[51] and *Wuchereria bancrofti *[52] is mediated in part by TT-specific IL-10. Alternatively, strong regulatory responses to helminth antigens associated with enhanced geohelminth antigen-induced IL-10 [80] may inhibit immune responses to unrelated vaccine antigens through bystander suppression.

### Potential effects of geohelminth infections on allergic sensitization

Childhood geohelminth infections are inversely associated with allergen skin test reactivity [81-87]. This observation has led to the suggestion that anti-parasite immune modulatory mechanisms may suppress allergic inflammatory responses to aeroallergens. However, the findings of intervention studies in which children infected with geohelminths have received anthelmintic treatment are contradictory. Different intervention studies have provided evidence for an increased incidence [88] or prevalence [55,89,90] of allergen skin test reactivity after periodic anthelmintic treatments, but a large cluster-randomized trial of periodic anthelmintic treatment in Ecuador did not observe a change in the prevalence of allergen skin test reactivity after treatment [91]. The contradictory findings of different studies could be explained by differences in the prevalence of geohelminth parasites between different geographic regions, the period for which anthelmintic treatment was given, the effects of early exposures to geohelminths in programming anti-allergic responses [5,39], or treatment effects on other endemic helminth infections (e.g. *Toxocara*).

The presence of geohelminths during pregnancy may modify the immune responses of offspring *in utero *[41]. The possible protective effects of environmental exposures such as geohelminths against allergy may be strongest when they occur in the first year or two of life [92]. We have hypothesized that early exposures to geohelminths may programme the infant immune system for reduced allergy [39]. Such programming may not be reversible (i.e. by anthelmintic treatment in later childhood) and could be 'reinforced' later by active regulatory mechanisms induced by heavy helminth infections (reversible by anthelmintic treatment) [39]. Evidence in support of this hypothesis has come from a recent observational study in Brazil showing that early and heavy exposures to *T. trichiura *protected against allergen skin test reactivity later in childhood independent of later infections [93].

The immunological mechanisms by which chronic geohelminth infections may suppress IgE-mediated hypersensitivity measured by allergen skin test reactivity are illustrated in Figure 3. Maternal geohelminth infections, augmented by infections in infancy, may have indirect suppressive effects on immediate hypersensitivity responses in the skin through effects on immune homeostasis. Chronic geohelminth infections in children are associated with an increased accumulation in vitro by unstimulated PBLs of the anti-inflammatory cytokine IL-10 [50]. A previous study of children from Cameroon infected with *A. lumbricoides *and *T. trichiura *provided evidence for an inverse association between geohelminth infection intensity and immune reactivity that was associated with enhanced production *in vitro *of IL-10 and TGF- β1 by unstimulated PBLs [94]. Further, a study of children in poor neighborhoods in Salvador, Brazil has shown that the presence of detectable spontaneous IL-10 is associated with poor access to sanitation [95] and geohelminth infections in early childhood [80]. Elevated 'homeostatic' production of IL-10 by immune cells may suppress immune reactivity [5]. IL-10 has been shown previously to suppress mast cell activation [96] and be inversely associated with wheal size to allergen skin tests [97].

In populations living in environments endemic for geohelminth infections, there is a strong disassociation between the presence of allergen-specific IgE in serum and skin test reactivity to the same allergen [57,82,98,99]. Environmental exposures including geohelminth infections are likely to be major determinants of this relationship. Geohelminth infections may affect the association between allergen-specific IgE in serum and skin test reactivity through enhanced production of helminth antigen-induced [54], aeroallergen-induced [53], or spontaneous IL-10 [50]. Increased IL-10, whatever the cellular source, may suppress mast cell activation in the skin, thereby reducing the prevalence of allergen skin test reactivity. The effects of maternal geohelminth or early infant infections on levels of allergen-specific IgE are not clear. A high proportion of children living in the rural Tropics appear to have low-affinity IgE to aeroallergens (e.g. 0.35-0.7 kU/L) that can be only be partially absorbed by pre-incubation with the specific allergen [98] and may represent cross-reactive anti-helminth IgE antibodies [100,101].

